### Sample size

Sample size calculations were performed for the primary outcome remission rates 12 weeks post first FMT/FMFT/placebo. The sample size calculation is based on a 2×3 table *χ*^2^ test as implemented in nQuery Advisor 7.0 (*χ*^2^ test of equal proportions in G groups (equal *n*’s)) even though a more complicated model will be used for the confirmatory analysis. Based on this, we estimate the remission rates 12 weeks post first FMT/FMFT to be *π*_FMT_ ≈30% or π_FMFT_ ≈30% while *π*_Placebo_≈5% are expected under placebo. To detect such a clinically relevant benefit at an overall power of 1 – *β* = 0.8 for a global significance level of *α* = 0.05 (two-sided), a sample size of *n* = 3 × 40 = 120 is required for the confirmatory analysis. To account for a potential dropout rate of 30% overall and/or lower power of the more advanced analysis model, the total sample size is *n* = 3 × 58 = 174 patients.

Table 1 shows the impact of slightly altered planning assumptions regarding the true rates on the global power. Moreover, the table also depicts power estimates for the joint test of FMT/FMFT against placebo and the two-group tests of FMT vs. placebo, FMFT vs. placebo (two group continuity corrected *χ*^2^ test of equal proportions; unequal and equal *n*). As similar rates are expected for FMT and FMFT, no power estimates are provided for this comparison.

**Table 1 Tab1:** Statistical power analysis

True rates [%]			Sample size per group (including dropouts)^a^	Power for the respective test setting [%]		
*π*_FMT_	*π*_FMFT_	*π*_Placebo_		Global test^b^	FMT and FMFT vs. placebo	FMT or FMFT vs. placebo
30	30	5	58	93	98	92
30	40	10	58	92	95	69 rsp 95
40	40	10	58	96	99	95

^a^Resulting in a total sample size would be 3 × 58 = 174, 3 × 93 = 279, and 3 × 50 = 150 patients to be randomized

^b^The increased power (i.e., a power larger than 80%) results from the inclusion of dropouts in the analysis

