### Statistical analysis

The main analysis will be conducted in the full analysis set according to the intention-to-treat principle. Remission rates will be compared with a two-step hierarchical testing procedure. In a first step, a generalized linear mixed model (GLMM) with fixed effects treatment and steroid/thiopurine stratum and random effect site will be applied to test the null hypothesis H_0_ that no difference in remission rates will be observed between the groups against the alternative in which there will be a difference between the groups. In case of rejection of H_0_, the following tests will be performed in a hierarchical order:
The FMFT and FMT group combined versus placeboFMT versus placeboFMFT versus placeboFMFT versus FMT

by means of Wald statistic on a two-sided significance level of 0.05. The significance level is met by this hierarchical testing approach.

Further sensitivity analyses in a per-protocol set, explorative subgroup analyses according to stratification levels, and analyses of secondary parameters with a respective GLMM approach are described in detail in the study protocol.

In principle, all data will be analyzed at least by descriptive statistics, i.e., number of available and missing data, mean, standard deviation, minimum, quartiles, and maximum for metric data and frequency analysis for categories.

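### The ordered confirmatory tests rest on Wald statistics although about 2 to 3 placebo remissions are expected; with none, they cannot reject however strong the effect

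*Protocol article*

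**What the plan says.** The Statistical analysis section of the protocol article says that a "generalized linear mixed model (GLMM) with fixed effects treatment and steroid/thiopurine stratum and random effect site will be applied" for the global null hypothesis. It continues: "In case of rejection of H_0_, the following tests will be performed in a hierarchical order". The order is both active arms combined against placebo, FMT against placebo, FMFT against placebo, then FMFT against FMT. These tests are done "by means of Wald statistic on a two-sided significance level of 0.05". The link function is not stated. The Wald wording attaches to the ordered tests, and no statistic is named for the global step.

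The Sample size section assumes 30% remission in each active arm, while about 5% "are expected under placebo". It sizes the trial on a 2×3 chi-square test, "even though a more complicated model will be used for the confirmatory analysis". One inflation, from 40 to 58 per arm, is meant to cover 30% dropout, lower power of the analysis model, or both. The Primary outcome section counts patients unavailable at week 12 as not in remission.

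**The concern.** A Wald test on the logit scale divides an estimated log odds ratio by its estimated standard error. When one group has almost no events, the standard error grows faster than the estimate. With no events the estimate is infinite and the ratio collapses to zero. Three of the four ordered tests need a finite placebo log-odds, and the fourth is reached only after those three. The better the active arms separate from a near-zero placebo arm, the more likely the test is to break down. What is at stake is a false-negative primary result in a trial whose data show a clear effect. The chi-square tests used for sizing do not behave this way, so the powers in Table 1 do not describe the tests that will be run.

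**Working it through.** **Inputs.** From Sample size: remission 30/30/5%, 58 per arm, 30% dropout. From Primary outcome: unavailable means no remission. From Statistical analysis: Wald, two-sided 0.05. Assumptions: logit link; no stratum or site effect; the combined contrast is the average of the two active log-odds minus the placebo log-odds. The adjusted mixed model itself was not simulated.

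**The plan's own figures.** For the global chi-square test the noncentrality is λ = n·Σ(pᵢ − p̄)²/[p̄(1 − p̄)]. With p̄ = 21.67%, λ = n × 0.04167/0.16972 = 0.2455n.
- n = 40: λ = 9.82, power 80.8%; 40 is the smallest n that reaches 80%.
- 40/0.7 = 57.1, rounded up to 58.
- n = 58: λ = 14.24, power 93.2% (Table 1: 93%).
- Continuity-corrected two-group tests: 98.2% combined and 92.2% single arm (Table 1: 98% and 92%).

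Table 1 reproduces, but for chi-square tests.

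**Expected placebo events.** 58 × 0.05 = 2.9. If the planning rates are completer rates and 30% drop out of every arm, they become 0.7 × 30% = 21% and 0.7 × 5% = 3.5%, and 58 × 0.035 = 2.0.

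**Chance of zero placebo remissions.** 0.95^58 = 5.1%; 0.965^58 = 12.7%; at 10% placebo, 0.90^58 = 0.2%.

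**What the tests return.** For one arm against placebo, z = [ln(x/(58 − x)) − ln(y/(58 − y))]/√(1/x + 1/(58 − x) + 1/y + 1/(58 − y)).
- 17, 17 and 0 remissions: the term 1/y is infinite. A fitted binomial model reports coefficient 23.7 and standard error 17,202, so z = 0.001 and p is about 1 for the global, combined and single-arm tests. Pearson global: Σ(O − 11.33)²/(58 × 0.1954 × 0.8046) = 192.7/9.12 = 21.1 on 2 df, p = 0.00003.
- 17 against 1: z = 3.163/1.049 = 3.01, p = 0.003. It rejects.
- 17 against 2: z = 3.16, p = 0.002. It rejects.
- 12 against 1 and 12 against 2: p = 0.011 and 0.012. Both reject.
- 10, 10 and 1: Wald global p = 0.058, Pearson global p = 0.012.

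**Power by exact enumeration of all outcomes** (58 per arm; a zero cell counts as Wald non-rejection; score means uncorrected Pearson):

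| True rates (%) | Step reached | Wald throughout | Score throughout |
|---|---|---|---|
| 30/30/5 | global | 92.1% | 98.0% |
| 30/30/5 | + combined vs placebo | 92.0% | 97.9% |
| 30/30/5 | + FMT and FMFT vs placebo | 87.3% | 93.9% |
| 21/21/3.5 | global | 66.4% | 87.7% |
| 21/21/3.5 | + combined vs placebo | 65.0% | 87.0% |
| 21/21/3.5 | + FMT and FMFT vs placebo | 52.1% | 75.9% |

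If the global step is Pearson and only the ordered tests are Wald, power through the combined test at 21/21/3.5 is 73%. Of the 22-point gap there (87.0 − 65.0), 12.7 points come from zero placebo events and 9.4 from non-zero counts (components rounded separately).

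**Direction.** With the active arms held at 30% and placebo falling through 5, 3.5, 2 and 1%, Wald power through the combined test falls through 92, 86, 69 and 44%. Score power rises from 98% to above 99.9%.

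**Size of the global test at a common 5% rate.** Wald 0.5%, score 4.2%, unpenalised likelihood ratio 7.8%. The score test's extra power is therefore not bought with excess type I error.

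**The case against.** A reader might infer that the trial is likely to fail, or that the planned test has far less power than the one used for sizing. The documents do not support either.

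- **Zero events is a minority outcome.** It has a 5.1% chance at the planning rate. The 12.7% needs 30% dropout in every arm and planning rates that apply to completers. Table 1 applies 30/30/5 to all 58 patients including dropouts, so those rates can also be read as already covering everyone randomized.
- **At 30/30/5 power holds up.** Wald gives 92% for the global test and 91% for FMT against placebo; Table 1 states 93% and 92%. Only the combined step is visibly lower (92% against 98%).
- **Dilution does part of the damage.** At 21/21/3.5 the plan's own chi-square formulas already give only 78% global and 74% single-arm power. Wald then gives 66% and 70%.
- **One or two placebo events do not defeat the test at the expected active rates.** With 17/58 on FMT, p stays at 0.002 to 0.003. Low counts such as 10, 10 and 1 can be lost, but only if the global step is Wald.
- **At 10% placebo, used in two of Table 1's three rows, the effect is small.** For 40% against 10%, single-arm power is 97.1% (Wald) and 97.6% (score).
- **The plan makes some allowance.** The step from 120 to 174 patients is partly for lower model power, and the error is conservative.

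All of this stands and limits the size of the point. It does not remove it. An unseen analysis plan may hold a rule for empty cells, but this article itself names the Wald statistic, so such a rule would have to override it. If the global step used another statistic, the first ordered test would still fail at zero events.

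**Conclusion.** The point holds in limited form: a stated confirmatory rule gives the wrong answer in a data pattern that the plan's own figures make possible. With zero placebo remissions (5.1% chance at 5%, 12.7% at 3.5%) no test against placebo can reject. The loss through the combined test is about 6 points at 30/30/5. At 21/21/3.5 it is about 22 points, or 14 (87 − 73) if the global step is Pearson. There the Wald chain falls below the 80% target while the score chain through the combined test stays above it.

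This rests on a logit link (log and probit share the problem; an identity link would behave differently), on an unadjusted model, and, for the diluted figures, on equal dropout in all arms with planning rates that apply to completers. The error can cause a false negative but not a false positive.

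**What to change.** Before unblinding, state that the global and ordered p-values come from one of two tests:

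- a score-type test, such as Cochran-Mantel-Haenszel; or
- a Firth-penalised likelihood-ratio test.

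The strata must be settled first, because the Randomization section gives two different sets of factors: site with prior biologics, and steroid/thiopurine use with centre. The mixed model can stay for estimation, but the plan should say that penalised estimates with profile-penalised confidence intervals are reported when a cell is zero or sparse, since the ordinary estimates diverge there. Do not move to the unpenalised likelihood-ratio test, whose global size is about 7.8% at a common 5% rate.

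The cost is a change of wording, with no extra patients. The one drawback is that the p-value is no longer read directly from the mixed-model output.

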## Discussion

The primary purpose of this study is to assess the effect of an Investigational Medicinal Product (IMP) intervention in patients with mild to moderate active ulcerative colitis. A stable engraftment of the transferred multi-donor microbiome or a stable modification of the patient microbiome is expected from long-term application over 12 weeks. The application of frozen encapsulated fecal microbiota (FM) or sterile fecal microbiota filtrate (FMF) allows a non-invasive at-home treatment which increases patient acceptance and compliance.

Numerous logistical challenges have to be resolved before starting the clinical study. In this context, patient safety is most important. Transmission of enteropathogens by FMT is a key safety issue (and feared complication). In 2019, two immune-compromised patients contracted ESBL *E. coli* infection after FMT from a common stool donor [29]. The Federal Institute for Drugs and Medical Device (BfArM) issued a safety alert in June 2019 regarding the use of FMT and the risk of serious adverse reactions due to transmission of multidrug-resistant organisms and screening for these pathogens was made standard practice after these instances worldwide [30, 31]. While exclusion testing for multi-resistant pathogens is established, the reliable exclusion of a clinically inapparent SARS-CoV-2 infection in donors is a challenge. Through the combination of repeated testing of potential stool donors (repeated nasopharyngeal swabs and stool examinations) with quarantining of the processed stool donation in a stool bank achieved the greatest possible safety. This concept is reinforced by accepting only COVID-19-vaccinated stool donors and participating patients. The frozen oral FM- or FMF-capsules are released from quarantine after the second tests of stool donors, 8 weeks after the first screening was passed.

The definition of threshold values for the microbiome diversity of the donors and a high similarity between the FM of the donor and the processed encapsulated FM act as an inclusion criterion for donors and as a quality standard for the production of FM-capsules. The definition of quality standards for the frozen FMF was resolved by setting a limit for the quotient for the concentration of bile acids in the dispenser stool versus that in the filtrate. However, the time-consuming setup of a mass spectral analysis of bile acids was necessary.

The delivery of the frozen IMP turned out to be a further logistical problem. Concerns regarding freeze–thaw cycles incurred by transport, the use of dry ice during the transport process, and home freezer conditions were addressed. According to the German Medicinal Products Act, IMPs may not be delivered from the manufacturer to the patient directly. Thus, a two-stage time-fixed delivery transport from the manufacturer to the patient with an in-between quality control in the test center by the study investigator was planned via a certified logistics company.

A major motivation for carrying out this clinical trial is the great interest shown by patients in this treatment concept. From numerous discussions with patients and representatives of self-help organizations, it becomes clear that they expect a more causal, but — above all — low-side-effect treatment approach in the future. Therefore, the patient’s perspective was already taken into account when planning the study. The current trial could therefore assign a concept of targeted microbiota modification as a future long-term treatment strategy of UC avoiding immunosuppressive therapy.

## Trial status

Protocol version number and date: version 03, 23.09.2021

The FRESCO trial is expected to start recruitment from May 2022 and recruitment is expected to finish in May 2024.

## Data Availability

Those involved in the FRESCO study have access to the final trial dataset and, upon request, the dataset can be made available to the participating test centers. The results will be uploaded to the EudraCT database and can also be published by the DRKS and clinical trials (register for studies). There are no restrictions regarding a publication of the data. Data protection for the patients is guaranteed.

## Abbreviations

AE: Adverse events
BfArM: Federal Institute for Drugs and Medical Device
CCS: Center for clinical studies
CDI: *Clostridioides difficile* infection
CM: Concomitant medication
CMV: Cytomegalovirus
COVID-19: Coronavirus disease 2019
CTCAE: Common Terminology Criteria for Adverse Events
DMSB: Data Monitoring and Safety Board
DRKS: German Registry for Clinical Studies
EBV: Epstein–Barr virus
FM(T): Fecal microbiota/microbiome (transfer)
FMF(T): Fecal microbiota/microbiome filtrate (transfer)
GCP: Good Clinical Practice
GMP: Good Manufacturing Practice
GLMM: Generalized linear mixed model
IBDQ: Inflammatory Bowel Disease Questionnaire
IMP: Investigational Medicinal Product
ITT: Intention to treat
PE: Physical examination
SARS-CoV-2: Severe acute respiratory syndrome coronavirus 2
SOP: Standard operating procedure
UC: Ulcerative colitis
VLPs: Virus-like particles
